### Primary outcome

#### Anatomical success (at 12 months)

Anatomical success (at 12 months) is objectified at 12 months follow-up using DUS. DUS is performed with the patient in the upright position, applying manual compression to the calf and using the Valsalva manoeuvre to detect flow and reflux. Occlusion is defined as a non-compressible vein (segment) that subsequently lacks flow and reflux. Recanalisation is defined as a compressible vein (segment) with flow or reflux.

Anatomical success outcomes (at 12 months) are defined as:

Anatomical success: complete occlusion of the treated vein segment or a recanalised segment of ≤5 cm.Anatomical failure:Partial recanalisation: a recanalised segment of >5 cm.Complete recanalisation: recanalisation of the entire treated vein segment.

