#### Anatomical success (during other follow-up moments)

Anatomical success (during other follow-up moments) is objectified at 1 week, 1, 6, 24 and 60 month(s) follow-up using DUS. DUS is performed with the patient in the upright position, applying manual compression to the calf and using the Valsalva manoeuvre to detect flow and reflux. Occlusion is defined as a non-compressible vein (segment) that subsequently lacks flow and reflux. Recanalisation is defined as a compressible vein (segment) with flow or reflux.

Anatomical success outcomes (during other follow-up moments) are defined as:

Anatomical success: complete occlusion of the treated vein segment or a recanalised segment of ≤5 cmAnatomical failure:Partial recanalisation: a recanalised segment of >5 cm.Complete recanalisation: recanalisation of the entire treated vein segment.

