#### Reinterventions

A reintervention is defined as a secondary treatment of the GSV in patients with anatomical failure after Flebogrif or EVLA treatment and assessed at 1 week, 1, 6, 12, 24 and 60 month(s) follow-up.

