#### Primary outcome analysis

Anatomical success at 12 months of follow-up is a dichotomous variable and will be described as numbers with percentages. The difference between the two groups will be presented as a percentage with a 95% CI. If the lower limit of this CI does not exceed the non-inferiority margin of −10%, the intervention will be considered to be non-inferior. A second analysis will be performed in which data from the last follow-up visit before a reintervention will be used in patients undergoing a reintervention of the GSV after failure of primary treatment.

These analyses will be performed for both the ITT and the PP population. Patients with missing data on the primary outcome parameters will be excluded from analyses.

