#### Secondary outcome analysis

Categorical variables (technical success, safety, anatomical success, complications, clinical success, reinterventions, AASV reflux and neovascularisation) will be described as numbers with percentages. Between-group differences will be analysed using the χ^2^ test or the Fisher’s exact test where appropriate.

Continuous variables that are single measurements (operation time, intraprocedural and postprocedural pain scores) will be described as means with an SD in the case of normally distributed data and as medians with an IQR in the case of a non-normal distribution. Between-group differences will be analysed using the independent samples t-test or the Mann-Whitney U test depending on the data distribution.

Continuous variables that are measured at several moments (VCSS, CEAP Clinical score, aesthetic result and VEINES-QOL/Sym) will be described as means with an SD in the case of normally distributed data and as medians with an IQR in the case of a non-normal distribution. Between-group differences and change over time will be analysed using a linear mixed model. This type of analysis handles missing data well, making imputation unnecessary.

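### The analysis that uses data from before a reintervention covers only the 12-month outcome, so at 24 and 60 months a re-treated, occluded vein meets the definition of success for the randomised device

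*Protocol article*

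**What the plan says.** Under Primary outcome analysis, the main 12-month comparison is of the outcome as observed: "Anatomical success at 12 months of follow-up is a dichotomous variable and will be described as numbers with percentages". One further analysis deals with re-treatment: "A second analysis will be performed in which data from the last follow-up visit before a reintervention will be used in patients undergoing a reintervention". The section then adds "These analyses will be performed for both the ITT and the PP population", which refers to the 12-month analyses just described.

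For the remaining visits, the secondary outcome section states "Anatomical success (during other follow-up moments) is objectified at 1 week, 1, 6, 24 and 60 month(s) follow-up using DUS". The definition of success is the same there as for the primary outcome: "complete occlusion of the treated vein segment or a recanalised segment of ≤5 cm". It describes the state of the vein on the day of the scan and does not mention re-treatment.

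Secondary outcome analysis covers these visits in one general sentence, "Categorical variables (technical success, safety, anatomical success, complications, clinical success, reinterventions, AASV reflux and neovascularisation) will be described as numbers with percentages", with a chi-square or Fisher's exact test between arms. No reintervention rule appears there.

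Under Reinterventions, "A reintervention is defined as a secondary treatment of the GSV in patients with anatomical failure after Flebogrif or EVLA treatment". This is a separate secondary outcome, assessed at every visit up to 60 months.

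**The concern.** By the protocol's own definition, every reintervention follows an anatomical failure of the first treatment. Yet the definition of success at later visits looks only at the current scan, so the same patient can be tabulated as a success at a later visit. The investigators evidently saw this at 12 months, since they planned a companion analysis for it. The later visits, by which time more failures may have been re-treated, have no counterpart.

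What is at stake is the meaning of the long-term figures. The article lists five-year follow-up among the trial's strengths, and readers will take the 24- and 60-month percentages as evidence on how durable Flebogrif is compared with EVLA. If re-treated veins are included as found, those percentages describe the first treatment plus any later re-treatment. For a given re-treatment share, the arm with more failures gains more.

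**Working it through.** **1. The plan's own figure.** The only calculation in the article is the 12-month sample size. With 95% v 93% success, a margin of 10 points, one-sided 2.5% and 80% power, (1.96 + 0.8416)² × (0.95×0.05 + 0.93×0.07) / (0.10 − 0.02)² = 7.849 × 0.1126 / 0.0064 = 138.1. That rounds up to 139 per arm, or 278. Then 139 / 0.9 = 154.4, giving 155 per arm and 310 in total. Both stated figures reproduce, and nothing below changes them.

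**2. How one patient is classified.** Take a patient whose vein is recanalised over more than 5 cm at 12 months, is then re-treated, and is occluded at 24 months.
- 12 months, main analysis: failure.
- Reinterventions: counted once re-treated.
- 24 months: occluded on duplex, so the definition of success is met.
- Arm: as randomised, under the intention-to-treat rule in the Data analysis plan.
- Follow-up: the Withdrawal section does not make a reintervention a reason to leave the study, so the 24-month scan is expected.

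If re-treatment came before 12 months, the main 12-month analysis would have the same exposure, but the second analysis would show the pre-reintervention status beside it. At 24 and 60 months nothing does so.

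**3. Effect on the rates.** Let p be the success rate of the randomised device alone, r the share of failures re-treated, and s the share of re-treated veins occluded at the visit. Then

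observed success = p + (1 − p) × r × s.

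If r and s are equal in both arms, observed gap = (1 − r×s) × true gap.

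**4. Illustrations.** The article gives neither r nor s, and no expected 24- or 60-month success rates. All values of r and s are therefore assumptions, with r from 25% to 100% and s from 90% to 95%. The 93% and 95% are the protocol's 12-month rates, carried forward as an assumption; 85% v 95% is an assumed larger gap.

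| Device alone, Flebogrif v EVLA | r | s | As observed | True gap | Observed gap |
|---|---|---|---|---|---|
| 93% v 95% | 25% | 90% | 94.6% v 96.1% | −2.0 | −1.6 |
| 93% v 95% | 50% | 90% | 96.2% v 97.3% | −2.0 | −1.1 |
| 93% v 95% | 100% | 95% | 99.7% v 99.8% | −2.0 | −0.1 |
| 85% v 95% | 50% | 90% | 91.8% v 97.3% | −10.0 | −5.5 |

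For the fourth row: 85 + 15 × 0.45 = 91.75, 95 + 5 × 0.45 = 97.25, and the gap is (1 − 0.45) × (−10) = −5.5. With r = 0 nothing changes.

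**5. Unequal re-treatment.** If the shares differ by arm, the single multiplier no longer applies. Assume failure of 15% (Flebogrif) v 8% (EVLA), with 60% v 30% of failures re-treated and closed. Observed failure is then 15% × 0.4 = 6.0% v 8% × 0.7 = 5.6%, so success reads 94.0% v 94.4%. The gap is −0.4 points where the true gap is −7. The document supports neither the failure rates nor the difference in re-treatment; the example shows direction only.

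**The case against.** A reader might infer that the protocol rules that re-treated veins count as successes, and that late durability will be overstated. The documents do not go that far. No sentence says how a re-treated vein is scored at 24 or 60 months; the result follows from applying the definition literally. A full protocol or analysis plan, not shown, may extend the rule. Overstatement also requires re-treatments that happen and hold: a re-treated vein recanalised over more than 5 cm is still a failure.

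A reader might also infer that the 12-month result is protected and only later visits are exposed. That is too strong. The pre-reintervention analysis is a second analysis, and the main non-inferiority comparison has the same exposure. The difference is that 12 months has a companion analysis and the later visits do not.

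The best defence is that reinterventions are a reported, tested outcome at the same visits, so masking would not go unseen. In the unequal example, at least 15% × 0.6 = 9% v 8% × 0.3 = 2.4% of patients would appear as re-treated. This stands in part: masking would be visible. But two separate percentages do not show how many of the successes were re-treated veins, and the between-arm test is still run on the uncorrected outcome.

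Finally, success as observed, whatever re-treatment was given, is a legitimate quantity. That is a reason to report it, but not to report it alone as durability of the device.

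**Conclusion.** The point holds in a limited form. The printed plan states a definition and a test for anatomical success at the other visits that, taken literally, credit a successful re-treatment to the randomised device, with no companion analysis like the one at 12 months. This can raise late success in both arms and pull the difference towards zero.

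The size cannot be computed from the document. Over the assumed ranges with 93% v 95%, Flebogrif success rises by 1.6 to 6.7 points and EVLA by 1.1 to 4.8. The gap shrinks from −2.0 to between −1.6 and −0.1, a shift of less than 2 points. A larger true gap loses more, as with −10 reading −5.5. These figures assume equal re-treatment and closure in both arms. A gap that nearly vanishes needs unequal re-treatment or near-complete successful re-treatment, and the documents establish neither.

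The affected outcomes are secondary and have no margin. The sample size, the power and the non-inferiority decision at 12 months do not depend on them. The change is worth making because the late figures are the trial's durability evidence and the data needed are already collected.

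**What to change.** In Secondary outcome analysis, extend the existing second analysis to anatomical success at 6, 24 and 60 months. A patient who has a reintervention of the great saphenous vein after failure of primary treatment keeps the pre-reintervention status, which is failure, at that visit and all later ones.

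Use the same definition in the 12-month second analysis. Otherwise a re-treated patient could be a failure at 6 months, a success at 12 and a failure again at 24. Naming the status as failure also removes any doubt where the failure was found between scheduled visits and the last scheduled scan still showed success.

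At each visit, report this percentage beside the as-observed one, labelled as assisted success. The main 12-month analysis and the margin can stay as they are.

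The cost is one sentence, one extra table row per visit, and slightly less favourable late success figures. No new data are needed, the sample size is unchanged, and the decision on whom to re-treat is not affected.

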#### Anatomical success

The calculation is based on the hypothesis that MOCA using Flebogrif will have no inferior anatomical success 12 months after treatment, compared with EVLA. The anatomical success rate in the EVLA group is expected to be 95%.^22^,^25^ The anatomical success rate in the Flebogrif group is expected to be 93%.^18^,^20^ A non-inferiority margin of −10% is applied. This margin is based on the anatomical success rate of 85% after MOCA using Clarivein.^14 25 26^ Taking into account a power of 80% and a significance level of 2.5% (one-sided test on the lower level of the 95% CI of the expected difference), 278 patients will be needed (https://www.sealedenvelope.com/power/binary-noninferior/). Corrected for 10% lost to follow-up, 155 patients need to be included in each treatment group. The total study population will consist of 310 patients.

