#### Postprocedural pain

Postprocedural pain is assessed daily during the first week after treatment using an 11-point NRS ranging from 0 (no pain) to 10 (worst pain imaginable).

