### Other measurements

Before treatment: gender (female or male); age; medical history (occurrence of migraine, asthma or chronic obstructive pulmonary disease, treatment of other leg vein(s)); use of platelet aggregate inhibitors; treatment side (right or left); baseline general pain score (assessed using an 11-point NRS ranging from 0 (no pain) to 10 (worst pain imaginable)); the presence of an (in)sufficient AASV and its confluence anatomy; GSV diameter (SFJ and mid-thigh) and length.During treatment: treated vein length; power in watts and total joules (EVLA); the amount of polidocanol foam used (Flebogrif); performance of concomitant phlebectomy of side branches.1 week, 1, 6, 12, 24 and 60 month(s) follow-up: treatment of side branches (phlebectomy and/or sclerotherapy (foam vs liquid, amount and percentage of polidocanol used)).

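### Postprocedural pain is scored daily for a week but classed as a single measurement, which leaves it out of the mixed model planned for repeated outcomes

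*Protocol article*

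**What the plan says.** Three parts of the Protocol article bear on this.

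- **Secondary outcomes, Postprocedural pain:** "Postprocedural pain is assessed daily during the first week after treatment using an 11-point NRS".
- **Secondary outcome analysis, second paragraph:** "Continuous variables that are single measurements (operation time, intraprocedural and postprocedural pain scores) will be described as means with an SD" or, if not normally distributed, as medians with an IQR. The comparison is then: "Between-group differences will be analysed using the independent samples t-test or the Mann-Whitney U test depending on the data distribution".
- **Secondary outcome analysis, third paragraph:** a separate class is set up, "Continuous variables that are measured at several moments (VCSS, CEAP Clinical score, aesthetic result and VEINES-QOL/Sym", and for that class "Between-group differences and change over time will be analysed using a linear mixed model". Postprocedural pain is not in the list.

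Table 1 marks postprocedural pain once, in the 1-week column. The outcomes sent to the mixed model are marked at screening and at every follow-up visit. Under Other measurements, a "baseline general pain score" on the same 0 to 10 scale is collected before treatment. Under Randomisation and blinding, allocation is stratified by surgeon (seven strata).

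**The concern.** A score taken every day for a week is repeated data. By the plan's own division it belongs with the outcomes analysed by mixed model, yet it is grouped with operation time and intraprocedural pain, which are each recorded once. A two-sample test needs one value per patient, and the article does not say how about seven become one.

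The outcome matters to readers. The Abstract gives less pain during and after the procedure as part of the case for mechanochemical ablation. The Introduction reports that two trials of another device found significantly lower pain scores and that other studies did not. On a disputed claim, the choice of day or summary can decide what is reported. The article gives no multiplicity rule for secondary outcomes.

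**Working it through.** **1. The plan's own figure.** The only computed figure is the primary sample size. Inputs, from the sample size section: "The anatomical success rate in the EVLA group is expected to be 95" per cent, "The anatomical success rate in the Flebogrif group is expected to be 93" per cent, margin 10 points, one-sided 2.5%, power 80%.

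n per arm = (1.960 + 0.842)² × (0.95×0.05 + 0.93×0.07) / (0.10 − 0.02)² = 7.849 × 0.1126 / 0.0064 = 138.1, rounded up to 139, so 278 in total. With 10% loss, 139/0.9 = 154.4, rounded up to 155 per arm and 310 in total. Both stated figures reproduce, and this point does not touch them.

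**2. Inputs for pain.** Seven daily values per patient follow from the outcome definition. The article gives no significance level for secondary outcomes and no between-day correlation. I assume two-sided 5% and correlations (ρ) from 0.5 to 0.9, with equal variance on each day.

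**3. Reading A: one test per day.** If the days were independent, the chance of at least one false positive is 1 − 0.95⁷ = 0.302. For correlated days, seven z-statistics were simulated (1,000,000 draws) under a common correlation and under a correlation that decays with the gap between days (AR(1)):

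| ρ | Common correlation | AR(1) |
|---|---|---|
| 0.5 | 23.0% | 26.7% |
| 0.7 | 17.8% | 22.5% |
| 0.9 | 11.4% | 14.8% |

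Across both structures the range is 11.4% to 26.7%. The Bonferroni level would be 0.05/7 = 0.0071.

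**4. Reading B: one chosen day.** There is one test at 5%, but six days are unused. With a common correlation, the variance of the 7-day mean relative to one day is (1 + 6ρ)/7. The smallest difference detectable with 80% power at 139 per arm, in single-day SD units, is (1.960 + 0.842) × √(2/139) = 0.336 for one day; for the mean it is that value times the square root of the variance ratio.

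| ρ | Variance ratio | Reduction | Detectable, one day | Detectable, 7-day mean |
|---|---|---|---|---|
| 0.5 | 4.0/7 = 0.571 | 43% | 0.336 | 0.254 |
| 0.7 | 5.2/7 = 0.743 | 26% | 0.336 | 0.290 |
| 0.9 | 6.4/7 = 0.914 | 9% | 0.336 | 0.321 |

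Under AR(1) the variance ratios are 0.348, 0.518 and 0.798, so the gain from averaging is larger.

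**5. Reading C: one summary per patient.** With a 7-day mean there is one test at 5% and every day is used. With complete data and a common correlation, its group contrast equals the average treatment effect from a mixed model. Neither problem arises; only the time course is given up.

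**The case against.** The strongest defence is Reading C. A weekly mean or area under the curve is one value per patient and is validly compared by t-test or Mann-Whitney. Table 1 can be read in its favour: pain has one mark, at the 1-week visit, and the mixed-model class may mean outcomes recorded at several visits. Which summary, and how missing diary days are handled, are details that an article commonly leaves to the full protocol or analysis plan. A Mann-Whitney test on a summary is also defensible for a bounded and possibly skewed 0 to 10 score.

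Much of this stands. A reader might infer that the plan must lead either to seven uncorrected tests or to a wasted diary. The text forces neither, because a single summary remains open. A reader might also fear that the daily values will be pooled as if they came from different patients; nothing in the article suggests that. Nor can it be concluded that the choice will be made after the data are seen, since a fuller document may settle it. Leaving out baseline pain and surgeon is a loss of efficiency in a randomised comparison, not an error.

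What does not stand is that this is only a missing detail. The article assigns the outcome to a class, and that class does not fit its own definition of the measurement. The single mark in Table 1 does not change a definition that makes the score daily. An analysis plan that follows the article inherits the mismatch; one that departs from it contradicts the published text.

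**Conclusion.** The point holds as an internal contradiction about one secondary outcome, and it should be corrected before analysis. Its size depends on the reading: about 11% to 27% chance of at least one false positive if each day is tested (30% if independent); a forgone variance reduction of about 9% to 43% if one day is used; nothing on either count if one weekly summary is used. These figures rest on the assumed correlations and significance level, and the variance range also on a common correlation between days. The false-positive range matters only if a claim could be made on any single day, and the article states no such rule.

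**What to change.** Move postprocedural pain to the linear mixed model already planned, with treatment, day, treatment-by-day, surgeon and baseline pain score. Prespecify one contrast, the average treatment difference over the first week, and show the daily values descriptively.

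Alternatively, keep it as a single measurement by naming the summary, such as the 7-day mean, compared between groups with adjustment for baseline pain and surgeon. Add a rule for missing diary days; the mixed model can use incomplete diaries without one, provided the gaps are missing at random.

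Either route makes the two sections agree. The cost is a change of wording: the daily scores, baseline pain score and surgeon stratum are already collected, and the sample size does not change.

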## Abstract

**Introduction:**

Endovenous laser ablation (EVLA) is associated with an excellent outcome in the treatment of great saphenous vein (GSV) incompetence. However, the use of thermal ablation requires tumescent anaesthesia and is associated with a risk of thermal damage. Mechanochemical endovenous ablation (MOCA) is a non-thermal ablation (NTA) alternative, which combines mechanical endothelial damage with the infusion of a sclerosant liquid or foam. Tumescent anaesthesia is not required. Preliminary experiences with MOCA using the Clarivein device show less intraprocedural and postprocedural pain and a faster clinical improvement compared with EVLA. Flebogrif (Balton, Poland) is a relatively new MOCA device. To determine the role of MOCA using Flebogrif, a well-designed, randomised controlled clinical trial of sufficient sample size and follow-up time is required. In this article, we provide the study protocol for the REBORN trial, aiming to demonstrate that MOCA using Flebogrif is not inferior to EVLA for the outcome of anatomical success in the treatment of GSV incompetence.

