Newer treatments modalities, especially non-thermal ablation (NTA) techniques, have potential benefits, such as increased patient acceptability and decreased risk of nerve injury. Currently, there are three NTA techniques that are widely discussed. Ultrasound-guided foam sclerotherapy (UGFS) has been used for some decades and avoids the risk of nerve injury. However, it is not as effective as endothermal ablation. Boersma *et al* reported pooled anatomical success rates of 63.6% after UGFS vs 98.5% and 97.1% after EVLA and RFA, respectively. Short-term clinical success and patient-reported outcome measures were comparable.^12^ Additionally, there is a very rare but well-documented risk of stroke after UGFS.^13^ More recently, two alternative NTA modalities have emerged. The first is cyanoacrylate closure using the VenaSeal Closure System or the VenaBLOCK Venous Closure System. Both devices enable the endovenous delivery of cyanoacrylate tissue adhesive to the vein causing fibrosis. A second alternative is mechanochemical endovenous ablation (MOCA), which combines mechanical endothelial damage with the infusion of a sclerosant liquid or foam. An example is the Clarivein device (Vascular Insights, USA), which combines a rotating wire causing endothelial damage with the injection of a sclerosant solution. The Clarivein device is studied and compared with endovenous thermal techniques in several randomised controlled trials. In both the MARADONA trial and Venefit versus Clarivein trial, pain scores were significantly lower in patients treated with Clarivein.^14 15^ However, these significant differences were not found in other clinical studies.^16 17^ Although overall, anatomical success is higher in patients treated with thermal ablation, similar improvements in clinical scores and QoL scores were found in all studies.^14^,^17^ However, the Clarivein device did not lead to widespread use.

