### Secondary outcomes

#### Intraprocedural pain

Intraprocedural pain is assessed during treatment using an 11-point Numeric Rating Scale (NRS) ranging from 0 (no pain) to 10 (worst pain imaginable).

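### The two pain comparisons leave the collected baseline pain score unused; adjusting for it may gain precision at almost no cost, provided the daily postprocedural scores first get a defined analysis

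*Protocol article*

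**What the plan says.** Under Other measurements, the protocol article lists among the pre-treatment data a "baseline general pain score (assessed using an 11-point NRS ranging from 0 (no pain) to 10 (worst pain imaginable". The two pain outcomes use a scale with the same range. For the first: "Intraprocedural pain is assessed during treatment using an 11-point Numeric Rating Scale (NRS) ranging from 0 (no pain) to 10 (worst pain imaginable". For the second: "Postprocedural pain is assessed daily during the first week after treatment using an 11-point NRS".

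Secondary outcome analysis places both outcomes in one class, "Continuous variables that are single measurements (operation time, intraprocedural and postprocedural pain scores", and says of that class: "Between-group differences will be analysed using the independent samples t-test or the Mann-Whitney U test depending on the data distribution". No covariate is named. The linear mixed model in the same section is reserved for VCSS, CEAP Clinical score, aesthetic result and VEINES-QOL/Sym.

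Randomisation and blinding stratifies on surgeon (seven surgeons) and on nothing else. The sample size section concerns anatomical success only. The article gives no power, standard deviation or correlation for pain.

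**The concern.** A two-sample t-test or Mann-Whitney test leaves in the error term whatever part of the pain outcome a patient's pre-treatment pain could explain. Entry requires symptomatic disease, so some patients plausibly have pain beforehand, and it may persist into the first-week scores. If so, the trial collects a useful covariate and does not use it.

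Precision on pain matters because pain is part of the rationale for mechanochemical ablation. The abstract says: "Preliminary experiences with MOCA using the Clarivein device show less intraprocedural and postprocedural pain and a faster clinical improvement compared with EVLA". The Introduction adds, after two trials that did find lower pain scores: "However, these significant differences were not found in other clinical studies". With conflicting evidence and no stated power for pain, a narrower interval would be useful.

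The same sentence of the plan raises a second issue. Postprocedural pain is scored every day for a week but analysed as though there were one value per patient. Until it is said which value that is, a covariate-adjusted model has no defined outcome to act on.

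**Working it through.** **The plan's own figure.** The only sample size given is for anatomical success, starting from "The anatomical success rate in the EVLA group is expected to be 95"%, with 93% for Flebogrif, a 10-point margin, one-sided alpha 2.5% and 80% power:

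n per arm = (0.95 × 0.05 + 0.93 × 0.07) × (1.960 + 0.842)² / (0.10 − 0.02)² = 138.1, rounded up to 139, so 278 in total. Allowing 10% loss, 139 / 0.9 = 154.4, rounded up to 155 per arm, so 310. Both stated totals reproduce. They do not bear on pain, except that they fix 155 per arm.

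**Inputs for pain.** From the article: 155 per arm, 1:1 allocation. Assumed: two-sided alpha 5%; rho from 0 to 0.5; and, only to express results in scale points, an SD of 2.

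**Formulas.**
- Unadjusted standard error in SD units: √(2/155) = 0.1136.
- Difference detectable with 80% power, unadjusted: (1.960 + 0.842) × 0.1136 = 0.318 SD, or 0.64 points at SD 2.
- Adjusting for baseline multiplies the variance by 1 − rho², and the interval width and detectable difference by √(1 − rho²).
- Adjusted power at that same difference: Φ(2.802 / √(1 − rho²) − 1.960).

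| Assumed rho | Variance removed | CI width factor | Power (80% unadjusted) | Adjusted n per arm matching 155 unadjusted | Detectable difference at SD 2 |
|---|---|---|---|---|---|
| 0 | 0% | 1.000 | 80.0% | 155 | 0.64 |
| 0.1 | 1% | 0.995 | 80.4% | 154 | 0.63 |
| 0.2 | 4% | 0.980 | 81.6% | 149 | 0.62 |
| 0.3 | 9% | 0.954 | 83.6% | 142 | 0.61 |
| 0.4 | 16% | 0.917 | 86.4% | 131 | 0.58 |
| 0.5 | 25% | 0.866 | 89.9% | 117 | 0.55 |

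Up to rho 0.3 the interval narrows by under 5% (1 − 0.954 = 4.6%) and power rises by 3.6 points. The power gain passes 5 points from about rho 0.4 and is about 10 points at 0.5.

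**Chance imbalance.** The planned tests use the raw outcome, so a baseline imbalance affects the estimate only through the baseline-outcome slope. A one-standard-error imbalance is 0.114 SD. With equal SDs and rho 0.3 it moves the estimate by 0.3 × 0.114 = 0.034 SD, about 0.07 points at SD 2. The unadjusted standard error already allows for this.

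**Consistency of the pain definitions.** The outcome definition gives one postprocedural score per day for the first week. The analysis section treats the outcome as measured once. No summary (mean, maximum or a chosen day) links the two.

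**The case against.** The case against is substantial, and most of it limits the size of the point.

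- The planned tests are valid under 1:1 randomisation and control type I error. This stands.
- Covariates for secondary outcomes are often left to an analysis plan, which is not shown here. That would answer an omission, but the article names the tests, and those tests admit no covariate.
- A reader might infer from the shared scale that precision is certainly being lost. The article does not support that. The baseline item is general pain, the outcomes are pain during and after a procedure, the entry criteria say symptomatic without mentioning pain, and no correlation is given. The loss could be negligible, especially for intraprocedural pain.
- Starting from exactly 80% power makes the gain look useful. At SD 2 and 155 per arm, a 1-point difference already has about 99% unadjusted power: Φ(1 / (2 × 0.1136) − 1.960) = Φ(2.44). Even at rho 0.5 the detectable difference improves by only 0.09 points (0.64 to 0.55).
- A reader might also infer that less pain is the benefit expected of Flebogrif. The cited experience is with Clarivein, a different device, and the article calls that evidence mixed. It states no pain hypothesis for Flebogrif, and its stated aim is non-inferior anatomical success.
- Patients know their allocation, and one might count that in favour of adjustment. It is not relevant: a baseline covariate does not remove reporting bias.

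What survives is that the data are already collected, and adjusting when rho is zero costs about one degree of freedom in roughly 310 patients for the baseline score. The potential gain outweighs that cost.

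**Conclusion.** The point holds as an optional efficiency improvement on two secondary outcomes. The plan fixes comparisons that cannot use a baseline score it already collects. Adjustment would remove 1% to 25% of the variance for rho between 0.1 and 0.5, with less than 5% off the interval width up to 0.3. Those correlations are assumptions; the article supports no particular value. The gain is probably larger for postprocedural pain.

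Nothing here shows bias, inflated type I error or any effect on the primary conclusion. Nor does a chance baseline imbalance pass in full into the estimated difference, as one might suppose; it enters only in proportion to the slope. The mismatch between daily scores and a single-measurement analysis does not depend on rho and has to be settled for the adjusted comparison to be defined.

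**What to change.** In Secondary outcome analysis:

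1. Make the main comparison of intraprocedural pain a linear model with treatment, the baseline general pain score and surgeon, reporting the adjusted mean difference with 95% CI.
2. Take postprocedural pain out of the single-measurement class. Analyse the daily first-week scores with a mixed model, or define a 7-day mean in advance and use the linear model above. Use the same covariates either way.
3. If residuals are clearly skewed, use robust standard errors or a proportional-odds model with the same covariates.
4. Keep the t-test or Mann-Whitney result as a sensitivity analysis.

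The cost is a few lines of analysis wording, settled before the pain data are analysed, and extra terms in an SPSS model. No new data are needed. The small downside is a rule for the few patients without a baseline score, for example imputing the overall mean of the covariate.
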